### Overview of study design

The current study will use a hybrid type I effectiveness-implementation approach to test implementation of an EHR-derived suicide risk model to facilitate identification, recognition, and engagement in supportive suicide prevention services among individuals who are estimated to be at risk for suicide and receiving services in behavioral health clinics at the participating health systems. This includes a stepped wedge cluster randomized trial design [31, 32] with randomization of behavioral health clinics into three waves across the three participating health systems. This design offers a novel approach to studying service delivery interventions as it provides a baseline period without implementation followed by random and sequential crossover of clinics from usual care control to intervention until all participating clinics are exposed. All clinics will have a pre-implementation phase (baseline period). Within that, just prior to implementation, health systems will train clinicians. Clinician training materials will be provided but sites will operationalize the training according to local customs and resources. Differences in training rigor provide additional variability as they may partially account for acceptability or feasibility. Implementation begins when each randomized clinic (stratified by site) transitions from usual care to running the risk model so clinicians can observe the risk indicator (the intervention is the enhanced care model with the suicide risk model and associated clinician notification). Analyses will examine within and between clinic variation in outcomes and account for time since implementation. This design allows implementation of the intervention at all clinics during the study period, a requirement of our clinical stakeholders; similar designs have been used in other suicide prevention trials [33, 34].

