Generalized Linear Mixed Models (GLMMs) with logit link function will be used to assess categorical outcomes (identification and recognition, separately, defined as yes/no) to study the effect of the intervention on identification and recognition. The results will be presented as odds ratios (OR) with 95% CIs. We will analyze the frequency of events identified through PHQ-9 (identification), recognized through the C-SSRS (recognition), or both combined. Additionally, GLMMs with a log link function will be used to separately assess the effects on identification and recognition by modeling the count of identified or recognized patients. The model will include the intervention (yes/no) as an independent variable to assess its effect while accounting for clustering and potential confounders. Among visits where individuals are identified or recognized as being at risk, we will further investigate factors influencing these outcomes, including patient demographics and clinical characteristics. The results will be presented as relative risk (RR) with 95% CIs. In these analyses, clusters will be analyzed according to their randomized crossover time. Models will include a random effect for cluster and a fixed effect for each phase, and will adjust for age, sex, race/ethnicity and cluster/clinic terms (i.e., secular trend). These models are optimal and commonly used for studies implementing stepped wedge cluster randomized trial designs [31, 32, 50]. All analyses will also adjust for time, given that the ratio of exposed clinics increases over time, and calendar month to account for seasonality of suicide attempts. Given that patients may be screened or identified as at-risk multiple times, the frequency of visits during the follow-up period will be adjusted in the model as well. In additional analyses, the model will account for cluster effects by clinic and correlation between repeated measurements for the same patient over time.

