These models will also be used to test mediators/mechanisms, given that we hypothesize that identification alone will not reduce suicide outcomes but rather increase the number of people receiving suicide intervention, which could lead to improvement (i.e., decrease) in suicide outcomes. Mechanisms include interaction with the alert and initiation of assessment, which starts the outpatient care pathway. We will also stratify analyses by health system site, and test for mental health diagnoses and prior suicide attempts as moderators. Importantly, we will exclude ‘training’ months for each phase of clinic implementation from the main analyses, since clinicians and patients may be partially exposed as the models are implemented and clinicians trained. In a secondary set of analyses, we will explore potential heterogeneity in treatment effects between clinics. Here we will conduct additional analyses to test within cluster comparisons of exposed and unexposed periods.

To examine the effectiveness of a suicide risk model on health service engagement and suicide attempt outcomes, we will start with similar descriptive and GLMMs analyses proposed previously for identification and recognition. The analyses here will focus on each unique health service engagement (supportive and crisis encounters separately) and suicide attempt outcomes, stratified by exposed (intervention) versus unexposed (control) groups. Suicide attempts will be captured by health system records using ICD-10 diagnosis codes occurring within the same 90-day and 180-day time periods. We will also use a Kaplan-Meier method and Cox-proportional hazards models to examine time-to-event for health service engagement and suicide attempts, with statistical adjustment for clinical and demographic factors. Individuals will be censored at the time of death or at 180 days past the index visit. We will again add terms for calendar month as well as site to account for variation by season and health system.

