Finally, we will separately examine the impact of health care engagement and exposure to ZS evidence-based interventions as mediators of suicide attempt and use of crisis services. We will estimate direct and indirect effects in our longitudinal settings using our previously proposed GLMMs [51]. Specifically, we will test the effect of the intervention (risk model study group, yes/no) on behavioral health service engagement (yes/no within 7 and 14 days via path ‘*a’*) and the effect of behavioral health service engagement on suicide attempt outcome (yes/no within 90 and 180 days via path ‘*b*’). The residual effect of the intervention unaccounted for by behavioral health service engagement will be tested via path ‘*c*’. We will also test a separate path model of exposure to documented suicide prevention interventions and their impact on suicide attempt outcomes using the same modeling approach. These models will include both individual documented supportive outpatient interventions for suicide and multiple interventions bundled together; we will also repeat these analyses for crisis services outcomes.

We will address missing data using multiple imputation or inverse probability weighting, depending on the nature and extent of missingness. Additionally, if the proportion of missing data is substantial, we will conduct sensitivity analyses to assess its potential impact on our findings.

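### The overview promises to account for time since implementation, but the stated model has one on/off intervention term, which does not estimate the average effect if the effect changes with exposure

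*Protocol article*

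**What the plan says.** Overview of study design makes a general commitment: "Analyses will examine within and between clinic variation in outcomes and account for time since implementation".

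Analysis plan for effectiveness outcomes then sets out the model, in the paragraph on identification and recognition. The treatment term is binary: "The model will include the intervention (yes/no) as an independent variable to assess its effect while accounting for clustering and potential confounders". The rest of the structure is: "Models will include a random effect for cluster and a fixed effect for each phase". Time enters with this reason: "All analyses will also adjust for time, given that the ratio of exposed clinics increases over time". Calendar month is added for seasonality.

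For service engagement and suicide attempts the same section says "we will start with similar descriptive and GLMMs analyses proposed previously for identification and recognition". The mediation models again test "the effect of the intervention (risk model study group, yes/no").

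On early exposure, the section says "we will exclude ‘training’ months for each phase of clinic implementation from the main analyses", because clinicians and patients may be partly exposed around that time. The overview places training inside the baseline period: "just prior to implementation, health systems will train clinicians".

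**The concern.** The reason given for the time term, that the share of exposed clinics rises, describes study-wide calendar time. It does not describe the time since a particular clinic switched. As written, the model has no exposure-time term and no interaction with time since go-live, so it does not do what the overview promises.

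This matters because the protocol gives reasons why the effect might change with use. Clinicians must notice a flag and act on it. Training is organised locally. Adaptations during the intervention period are expected. Acceptability is surveyed before go-live and again six months after. The authors also hypothesise that identification alone will not lower suicide outcomes, so any effect has to pass through uptake of care.

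In a stepped wedge with period effects, the on/off coefficient is a weighted sum of the effects at each exposure time, and those weights are not the shares of exposed clinic-time. An effect that grows would be understated and one that fades overstated.

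**Working it through.** The plan gives no figure on this point to reproduce. The check derives the weights that the on/off model places on each exposure period.

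**Inputs from the protocol.** 10 + 4 + 39 = 53 clinics (Study settings). Three waves, 395,000 patients, 2.5 years and ICC 0.01 (Sample size and power analysis). Waves three to six months apart (Clinic randomization and eligibility).

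**Assumptions.** Ten quarterly periods; waves of 18, 18 and 17 clinics; go-live at quarters 5/6/7 (3-month steps) or 5/7/9 (6-month steps), as the timeline figure is not shown; 395,000 / (53 × 10) ≈ 745 patients per clinic-quarter; ICC 0.01, with 0.001 as a variant; a linear model with random clinic intercepts in place of the logit or log GLMM.

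**Formula.** Let D hold the period indicators and the on/off term, V the clinic covariance, and E the indicators of exposure quarter 1, 2, and so on. The expected on/off estimate is Σ w(k)·δ(k), where δ(k) is the effect in exposure quarter k and w is the on/off row of (ΣD′V⁻¹D)⁻¹ ΣD′V⁻¹E.

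**Weights at ICC 0.01, with each quarter's share of exposed clinic-quarters:**

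| Exposure quarter | 1 | 2 | 3 | 4 | 5 | 6 |
|---|---|---|---|---|---|---|
| 3-month steps, weight | 0.884 | 0.289 | 0.000 | 0.000 | −0.086 | −0.087 |
| 3-month steps, share | 0.199 | 0.199 | 0.199 | 0.199 | 0.135 | 0.068 |
| 6-month steps, weight | 0.534 | 0.534 | 0.071 | 0.071 | −0.105 | −0.105 |
| 6-month steps, share | 0.248 | 0.248 | 0.168 | 0.168 | 0.084 | 0.084 |

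Each row sums to 1, so a constant effect is estimated without bias.

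**Four-quarter linear build-up** (0.25, 0.5, 0.75, 1, 1, 1):
- 3-month steps: 0.25 × 0.884 + 0.5 × 0.289 + 0 + 0 − 0.086 − 0.087 = 0.19. True average: 0.199 × (0.25 + 0.5 + 0.75 + 1) + 0.135 + 0.068 = 0.70.
- 6-month steps: 0.25 × 0.534 + 0.5 × 0.534 + 0.75 × 0.071 + 0.071 − 0.210 = 0.31. True average: 0.65.

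**Two-quarter build-up** (0.5, then 1):
- 3-month steps: 0.5 × 0.884 + 0.289 − 0.173 = 0.56. True average: 1 − 0.5 × 0.199 = 0.90.
- 6-month steps: 0.5 × 0.534 + 0.534 + 0.142 − 0.210 = 0.73. True average: 1 − 0.5 × 0.248 = 0.88.

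At ICC 0.001 the four-quarter results are 0.21 and 0.34, and the two-quarter results 0.57 and 0.74. A cluster autocorrelation of 0.8 instead of 1 moves any of these by about 0.01.

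**Fading effect** (full in quarter 1, falling evenly to 0.25 by quarter 4): the on/off model returns 1.04–1.06 against 0.55 with 3-month steps, and 0.91–0.94 against 0.60 with 6-month steps.

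**Training-month exclusion.** Monthly version over 30 months, ICC 0.01, go-live at months 13/16/19 or 13/19/25. Each cell is the on/off estimate against the true average over the months kept:

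| Months dropped | 3-month build-up, 3-month steps | 3-month build-up, 6-month steps | 6-month build-up, 3-month steps | 6-month build-up, 6-month steps |
|---|---|---|---|---|
| None | 0.71 vs 0.93 | 0.82 vs 0.92 | 0.36 vs 0.83 | 0.55 vs 0.79 |
| One before go-live | 0.63 vs 0.93 | 0.80 vs 0.92 | 0.29 vs 0.83 | 0.51 vs 0.79 |
| First one after | 0.88 vs 0.98 | 0.93 vs 0.97 | 0.49 vs 0.88 | 0.67 vs 0.85 |
| First two after | 1.00 vs 1.00 | 1.00 vs 1.00 | 0.62 vs 0.92 | 0.78 vs 0.90 |

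Dropping months before go-live does not help. Dropping months after it helps a lot when the build-up is short.

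**Precision of the alternative.** With effects for exposure quarters 1, 2, 3 and 4+, the standard error of the exposure-time average, relative to the on/off standard error, is 1.13–1.18 with 6-month steps and 1.37–1.53 with 3-month steps. The lower end of each range is an equal-weight average at ICC 0.001. The upper end weights by exposed clinic-quarters at ICC 0.01. With one indicator per exposure quarter the last figure rises to 1.68.

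**The case against.** The best defence is that the overview already commits to exposure time, that phase is undefined in the article, and that how the term is coded is a detail for an analysis plan. Part of this stands: an unseen plan could contain the term. But the article goes beyond leaving the detail open. It names a binary treatment term, repeats that coding for mediation, and justifies its time term on calendar grounds. The planned look at heterogeneity concerns differences between clinics, and the survival models run from the index visit, so neither addresses time since go-live.

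The second defence is the exclusion of training months, which is an explicit guard against partial early exposure. This stands in part. If the excluded months include the first ones after go-live and the build-up is short, the bias is small or nil. The overview, however, puts training before go-live, while the analysis section speaks of exposure as the models are implemented, so the reader cannot tell which applies.

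Third, no build-up curve is documented, and the intervention is a flag switched on at a defined moment. This stands. A reader might infer from the four-quarter figures that the suicide-attempt result will be badly wrong, or that a year-long build-up is the likely case. The document supports neither; it makes a changing effect plausible and says nothing of its shape.

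Fourth, the binary term is stated for identification and recognition and reaches suicide attempts only through the word similar. That is true, but no other model for suicide attempts is specified.

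**Conclusion.** The inconsistency is real and lies in the current text: the overview promises an adjustment that the stated model does not contain. The consequence is conditional. For an effect that builds up over two to four quarters, the on/off estimate would be 0.19–0.74 of the full effect where the true average is 0.65–0.90; for a fading effect it would be too large. These sizes rest on assumed go-live quarters, assumed curves and a linear approximation, and a logit or log GLMM will differ somewhat.

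It would go too far to conclude that the on/off model must be replaced as the main analysis. It is unbiased for a constant effect and more precise, which counts for an outcome anticipated at 0.6%. What the document does not support is reading a null on/off result, by itself, as absence of effect.

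**What to change.** Bring the analysis section into line with the overview:

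- Prespecify, beside the on/off model, a model with separate effects by time since go-live (for example quarters 1, 2, 3 and 4+), with the period effects kept.
- Report its exposure-time average for suicide attempts, and say how that average is weighted.
- State that a null on/off result will not be interpreted as no effect without this companion estimate.
- Reconcile the two sections on whether the excluded training months fall before or after go-live, and how many there are.

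The cost is some wording, a few model terms and the loss of precision shown above, which is larger with 3-month steps. Which of the two estimates is the headline is for the sponsor to decide; it should be settled before outcome data are examined.

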### Sample size and power analysis

We anticipate including > 50 clinics and approximately 395,000 unique behavioral health patients across three sites over a 2.5-year period, leading to over 1 million patient visits. We project that approximately 4–5% of patients will be identified as high risk and thus eligible for the intervention. Utilizing a stepped-wedge cluster randomized controlled trial design, with > 50 clinics randomly assigned across three waves, we will assess the primary outcome, suicide attempts, at 90- and 180-days post-intervention. Given an anticipated suicide attempt rate of 0.6% (*n* = 2,370) within 90 days of a visit, a 0.01 intraclass correlation coefficient within waves, we expect to achieve more than 80% power (2-sided *p* <.05) to detect an effect size corresponding to a 1.5% absolute difference in suicide attempt rates [47–49].

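### The main mixed model has one random effect per clinic and no clinic-by-period term, so its standard error is too small if clinics drift independently, by an amount that depends on inputs the protocol does not state

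*Protocol article*

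**What the plan says.** The protocol article, Analysis plan for effectiveness outcomes, sets out the models for identification and recognition: "Models will include a random effect for cluster and a fixed effect for each phase". The same sentence continues that they "will adjust for age, sex, race/ethnicity and cluster/clinic terms (i.e., secular trend". Further adjustment is made for time, calendar month and visit frequency. The article then endorses the structure: "These models are optimal and commonly used for studies implementing stepped wedge cluster randomized trial designs". In additional analyses, "the model will account for cluster effects by clinic and correlation between repeated measurements for the same patient over time".

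The same section reaches service engagement and suicide attempts, the primary outcome, by reference: "we will start with similar descriptive and GLMMs analyses proposed previously for identification and recognition".

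Sample size and power analysis gives a single correlation, "a 0.01 intraclass correlation coefficient within waves". It does not say on which scale, and it gives no correlation between periods.

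**The concern.** Clinics are the randomized units, and each is observed over several periods. With one random intercept per clinic, two patients of the same clinic are taken to be equally correlated whether they are seen in the same period or more than a year apart. Once the shared phase effect is removed, a clinic is assumed to have a constant underlying level.

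A stepped wedge draws much of its information from within-clinic change. Any clinic-specific movement between periods therefore enters the error of the intervention estimate directly, and it does not shrink as visits accumulate. A binomial or Poisson mixed model has no free residual variance to absorb it, so the reported standard error omits it. At stake is the type I error of the main tests. This is separate from same-patient correlation, because it remains with one visit per patient.

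**Working it through.** **The plan's own figure.** 0.006 × 395,000 = 2,370 events, as the article states. For the 1.5-point difference, power in the full sample is about 1.00 with or without a clinic-by-period term. This agrees with "we expect to achieve more than 80% power", but only as an inequality.

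**Inputs from the article.** Clinics 10 + 4 + 39 = 53 (Study settings); three waves; 395,000 patients; 1,000,000 visits; attempt rate 0.6%; ICC 0.01; two-sided 0.05. For an identification-type outcome I used 4.5%, the middle of the projected 4–5% flagged as high risk.

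**Assumptions.** Four equal periods, clinic size constant over time, critical value 1.96, and CAC from 0.5 to 1.

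**Variance components.** Let τ² be the total clinic variance and ω² = (1 − CAC)τ² the clinic-by-period part.
- Logit scale: τ² = (0.01/0.99) × π²/3 = 0.0332. At CAC 0.8, ω² = 0.2 × 0.0332 = 0.0066.
- Proportion scale: between-clinic SD = √(0.01 × 0.006 × 0.994) = 0.0077, or 0.77 points against a mean of 0.6. Then CV² = 0.01 × 0.994/0.006 = 1.66 and the log-scale variance is ln(2.66) = 0.98, about 29 times the logit-scale value.

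**Shortcut for equal clinics.** Let v be the sampling variance of one clinic-period. If the estimate rests on within-clinic change, type I error ≈ 2Φ(−1.96/√(1 + ω²/v)). Patients per clinic-period: 395,000/(53 × 4) = 1,863. Visits: 1,000,000/212 = 4,717. At CAC 0.8:
- Identification, logit: v = 1/(1,863 × 0.045 × 0.955) = 0.0125; ω²/v = 0.53; 2Φ(−1.96/1.24) ≈ 11%.
- Attempts by patient, logit: v = 1/(1,863 × 0.006 × 0.994) = 0.090; ω²/v = 0.07; 2Φ(−1.96/1.04) ≈ 6%.
- Attempts by visit, logit: v = 1/(4,717 × 0.006 × 0.994) = 0.0355; ω²/v = 0.19; 2Φ(−1.96/1.09) ≈ 7%.
- Attempts by patient, proportion scale, dividing through by p(1 − p): v = 0.99/1,863 = 0.00053; ω² = 0.002; ω²/v = 3.8; 2Φ(−1.96/2.18) ≈ 37%.

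**Why unequal sizes matter.** Henry Ford Health has 60/168 = 36% of annual patients in four clinics, so 395,000 × 60/168/16 ≈ 8,817 patients per clinic-period. For identification, v = 1/(8,817 × 0.045 × 0.955) = 0.0026, and the omitted variance is about 2.5 times the sampling variance. At HealthPartners, 395,000 × 58/168/156 ≈ 874 patients, v = 0.027, and the ratio is about 0.25. The stated model gives the large clinics too much weight.

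**Full generalized least squares calculation** of the stated model under a nested-exchangeable truth; type I error, equal/unequal clinics:

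| Outcome | ICC scale | CAC 0.8 | CAC 0.5 |
|---|---|---|---|
| Identification-type, 4.5%, by patient | logit | 11/18% | 19/32% |
| Attempts by patient | logit | 5.5/6.5% | 6/9% |
| Attempts by visit | logit | 7/9% | 10/16% |
| Attempts by patient | proportion | 37/52% | 54/67% |

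At CAC 1 every entry is 5%. At CAC 0.95 identification is 7/8% and the proportion-scale case 16/26%.

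**Simulation check** (logit mixed model, adaptive quadrature, 300 trials per setting, Monte Carlo error about 1.3 to 3 points). Identification gave 10/20% at CAC 0.8 and 20/31% at CAC 0.5. Attempts by patient gave 5/6% and 7/7%, and by visit 6/9% and 8/15%. Attempts with the proportion-scale clinic variance gave 46/58% at CAC 0.8.

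**The case against.** **Everything turns on a CAC that the article does not give.** This stands. At CAC 1 the stated model holds its level, so the size must be given as a range.

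**The ICC scale is open, and the logit scale suits a logit model.** This also stands. A reader might infer that the primary analysis rejects far too often, at rates of 40% to 65%. Rates of that order for attempts need a clinic variance far above the logit-scale reading of 0.01. Taking 0.01 on the proportion scale makes the between-clinic SD larger than the mean attempt rate. On the logit scale, inflation for attempts by patient is small.

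**The wording on clinic terms and secular trend may mean clinic-specific trends,** and the design overview promises to look at variation within and between clinics. The phrase can be read that way, but it is too unclear to specify a term. Linear clinic trends would not capture irregular period-to-period shifts. The planned analysis of heterogeneity between clinics concerns treatment effects and is secondary.

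**Much of the change described is system-wide.** The Zero Suicide updates are described for whole health systems. Drift shared across a site would not be captured by independent clinic-by-period effects either, so this fix does not address it.

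**Covariance detail belongs in the SAP.** A missing detail would be no finding. Here the article positively states a structure and calls it optimal, and following that text produces the problem. The link to attempts is looser, since it rests on similar models.

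**Conclusion.** The point holds in conditional form. The stated model is valid only if clinics do not drift independently, which the article neither states nor justifies. If they do drift, the error is always towards too many rejections.

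At CAC 0.8 the effect is clear for identification-type outcomes, which the quoted sentence governs directly. It is slight for attempts by patient and modest by visit, with the ICC on the logit scale. It is severe for attempts only under the proportion-scale reading. The unequal-size figures are closer to this trial, because average clinic size runs from about 1,490 patients a year (58,000/39) to 15,000 (60,000/4).

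A reader might also infer that the sample size claim fails. It does not fail on this ground: power for the literal 1.5-point difference is about 1.00 either way. That a reduction of 1.5 points from 0.6% is impossible is a separate matter.

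**What to change.** In Analysis plan for effectiveness outcomes:
- Add a clinic-by-period random effect, or a discrete-time decay correlation, to the main mixed models for identification, recognition, service engagement and suicide attempts.
- Report a clinic-level robust standard error with small-sample correction as a check. One simulation of the added-term model for attempts (120 to 320 replicates) rejected in about 3–9%, so calibration should not be taken for granted.
- Replace the phrase on clinic terms and secular trend with an explicit list of the time terms, saying which are common and which are clinic-specific.

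In Sample size and power analysis, state the ICC at clinic level instead of within waves, give its scale, and give an assumed CAC range.

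The cost is one more variance component and somewhat wider intervals, with no new data. At CAC 0.8, by patient (equal to unequal clinics), the corrected standard error is 1.02 to 1.05 times the stated model's for attempts and 1.22 to 1.32 times for identification, both on the logit scale. It is 2.14 to 2.24 times for attempts under the proportion-scale reading. If drift is absent, the added variance should be estimated near zero and little is lost.

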**Methods:**

This hybrid type I effectiveness-implementation pragmatic clinical trial will test a suicide risk identification model in behavioral health clinics at three large health systems. Local decision-makers will determine implementation specifics at each site. Clinics within each health system will be randomized to determine order of implementation. A stepped-wedge design using repeated measures pre/post-implementation maximizes statistical efficiency and power with fewer participants compared to a parallel design while allowing all clinics to participate. A pre-implementation period will serve as the baseline. The primary outcome will be the rate of suicide attempt per 1000 visits at 90- and 180-days following a behavioral health visit in which an individual was identified by the suicide risk model compared with the baseline period (no use of suicide risk model). Secondary outcomes include identification of suicide risk and recognition of individuals at risk for suicide (e.g., completed risk assessment), both compared to the baseline period. Generalized linear mixed models will be used to account for clustering within clinics and repeated measures over time, adjusting for relevant covariates to estimate the effect of the suicide risk model on outcomes. Implementation outcomes, including system-level determinants and clinician acceptance and use of the suicide risk model, will also be measured.

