### Analysis plan for effectiveness outcomes

We will analyze outcomes, for both: (1) unique patients, defined as those new to the study sample without a visit in the past three months, and (2) unique visits, where each health care encounter is considered separately, allowing for multiple visits per unique person, given that patients may be screened or identified as at-risk at multiple visits.

Only study biostatisticians will have access to the final trial datasets. We will begin with descriptive analyses of the study sample, including patient demographic characteristics, encounters, history of past-year suicide attempt, and current mental health diagnoses by exposure group. Descriptive analyses will also examine each of the individual identification and recognition measures using health system records, stratified by exposed (intervention) versus unexposed (control) periods. We will calculate the clinic/cluster sizes for each phase of implementation and clinic/cluster characteristics by exposure period to assess balance across the study period. Standard chi-square tests and t-tests will be used to compare variation in each outcome variable between exposure groups, and in each unique phase of implementation. We will then plot change in both counts and proportions of each individual outcome graphically by study exposure period.

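### The per-visit suicide-attempt model has only a clinic random effect and leaves same-patient correlation to supplementary analyses, so its intervals will be too narrow by an amount the protocol does not fix

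*Protocol article*

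**What the plan says.** All places are in the protocol article.

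- **Outcome and unit.** The abstract and the section on study measures define the primary outcome as suicide attempts per 1000 visits, within 90 or 180 days of a behavioral health visit. The denominator is all visits.
- **Two analysis units.** The analysis plan for effectiveness outcomes names unique patients (no visit in the past three months) and unique visits, and does not rank them. For visits, "each health care encounter is considered separately, allowing for multiple visits per unique person".
- **Model.** For identification and recognition, "Models will include a random effect for cluster and a fixed effect for each phase". Covariates include visit frequency during follow-up.
- **Same-patient correlation.** It appears only afterwards: "In additional analyses, the model will account for cluster effects by clinic and correlation between repeated measurements for the same patient over time".
- **Carry-over to attempts.** The same section says the attempt analyses will start with similar mixed models. It restates no random effects and adds no patient term.
- **Abstract.** "Generalized linear mixed models will be used to account for clustering within clinics and repeated measures over time". It names no patient-level term and does not make this a supplementary step.
- **Volume.** The sample size section expects "approximately 395,000 unique behavioral health patients across three sites over a 2.5-year period, leading to over 1 million patient visits".

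**The concern.** A patient seen several times within a few months contributes several overlapping outcome windows. A single attempt then makes every visit in the preceding 90 or 180 days an event. These records are close to duplicates. A clinic random effect captures only what all patients of a clinic share, so the model treats a patient's visits as independent once the clinic is known. Adjusting for visit frequency changes the modelled mean and leaves the covariance as it was.

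The article aggregates identification and recognition per individual because visits repeat, but states no such step for attempts, where the overlap matters most. If the order of analyses is followed as written, the main per-visit result on suicide attempts carries an interval that is too narrow and a test that rejects a true null more often than 5% of the time.

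**Working it through.** **Inputs from the document.** 395,000 patients; over 1,000,000 visits; 2.5 years; attempt rate 0.6% within 90 days; windows of 90 and 180 days; over 50 clinics in three waves. The settings section lists 10 + 4 + 39 = 53 clinics. The stated intraclass correlation of 0.01 refers to waves; no within-patient correlation is given.

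**The plan's own figure.** 395,000 × 0.006 = 2,370, as stated. This is a count per patient, although the outcome is per visit. If 0.6% held per visit, 1,000,000 × 0.006 = 6,000 visits would be positive, and they would come from fewer than 6,000 attempters.

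**Visits per patient.** 1,000,000 / 395,000 = 2.53. Since the visit total is a lower bound, so is this.

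**Formulas.** With design effect DE, the standard error is understated by the factor √DE, and the true size of a nominal 5% test is 2[1 − Φ(1.96/√DE)].

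**Check 1: exchangeable correlation, equal visit counts.** DE = 1 + (2.53 − 1)ρ, with ρ assumed.

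| ρ | DE | SE factor | Type I error |
|---|---|---|---|
| 0.1 | 1.15 | 1.07 | 7% |
| 0.5 | 1.77 | 1.33 | 14% |
| 0.9 | 2.38 | 1.54 | 20% |

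Uneven visit counts raise this. With a coefficient of variation of 1 and ρ = 0.5, DE = 1 + (2 × 2.53 − 1) × 0.5 = 3.03, an SE factor of 1.74.

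**Check 2: simulated overlapping windows, variance of the overall per-visit rate.** Visits per patient are 1 plus a negative binomial count (mean total 2.53, dispersion 0.5 to 3). Visit dates are uniform over an assumed span and attempt dates are uniform. DE is the patient-clustered variance divided by the naive variance.

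| Span of a patient's visits | DE, 90 days | SE factor | Type I error | DE, 180 days | SE factor | Type I error |
|---|---|---|---|---|---|---|
| 180 days | 2.0–2.6 | 1.4–1.6 | 17–22% | 2.7–3.7 | 1.6–1.9 | 23–31% |
| 2.5 years | 1.2–1.4 | 1.1–1.2 | 7–10% | 1.4–1.7 | 1.2–1.3 | 10–13% |

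A one-year span lies between: DE 1.5 to 1.9 for 90 days and 2.0 to 2.6 for 180 days.

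**Check 3: the treatment contrast itself.** A null stepped-wedge simulation used 51 clinics, three waves, 40,000 patients, about 2.5 visits each and 90-day windows. It fitted a linear model with clinic and month effects, with 150 runs per setting.

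| Days between visits | True SE / naive SE | Coverage of naive 95% interval | Coverage, patient-clustered SE |
|---|---|---|---|
| 14 | 1.54 | 80% | 96% |
| 30 | 1.30 | 84% | 98% |
| 60 | 1.10 | 92% | 95% |

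This allows for patients with visits on both sides of crossover, which pulls the other way. The naive interval was still too narrow in every setting. With 150 runs, each coverage figure is uncertain by a few percentage points.

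**The case against.** Four points deserve weight.

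1. **The random effects of the attempt model are not restated.** The clinic-only model is set out for identification and recognition; for attempts the text says only that similar models are the starting point. The abstract could be read as promising more, and a covariance structure is often left to an analysis plan that is not shown here. This stands as a limit on certainty. But the article does more than stay silent: it assigns an order, with same-patient correlation second, and carries the approach over to attempts without changing it.

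2. **The remedy is already planned.** This stands. A reader might infer that the plan ignores repeated visits altogether, and the text does not support that. The defect is which model leads.

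3. **A unique-patient analysis runs in parallel.** This stands too. It is largely free of the problem, although re-entry after three months can still overlap a 180-day window. The two units are not ranked, and the primary outcome is defined per visit.

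4. **The size depends on assumptions.** This is correct. A reader might infer that standard errors are understated by 1.4 to 1.9 and that type I error is 17% or 26% (DE of 2 or 3). Those figures need visits concentrated within about six months, or strongly uneven counts. The article gives about 2.5 visits over 2.5 years, which allows much smaller values. The upper figures also describe a single overall rate; for the stepped-wedge contrast with 90-day windows the factor was 1.10 to 1.54.

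A reader might also object that a single clinic intercept assumes clinic correlation never decays over time. Nothing in the document shows how much that matters, so it forms no part of this point.

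**Conclusion.** The point holds for the per-visit analysis of suicide attempts. Followed as written, the order of models puts a too-narrow interval first and the adequate one second, and it does not match the abstract. The direction was the same in every setting examined.

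At about 2.5 visits per patient, the standard error is understated by a factor of about 1.1 to 1.6 for 90-day windows (type I error about 7% to 22%) and about 1.2 to 1.9 for 180-day windows (about 10% to 31%). The low end is for visits spread over the full 2.5 years. The high end is for visits within about six months with skewed counts.

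The range rests on assumed visit spacing, visit-count skew and uniform attempt dates. The treatment contrast was checked for 90-day windows only, with a linear rather than a logit model; the 180-day range comes from the overall rate. The document does not say where in the range this trial lies. The conclusion does not extend to the unique-patient analysis, or to identification and recognition where those are aggregated per individual.

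**What to change.** - Make the main per-visit attempt analysis account for same-patient correlation. Either nest a patient random effect in clinic, or keep the stated fixed effects and use clinic-level cluster-robust standard errors with a small-sample correction for the 53 clinics listed. The robust option needs no assumption about how correlation falls as visits move apart, and it may be easier to fit with a rare outcome and few visits per patient.
- Keep the clinic-intercept-only model as a sensitivity analysis.
- State the random effects of the attempt model explicitly, and bring the abstract and the analysis plan into line on repeated measures.

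The cost is wording, some computing time and wider intervals. No design change or new data is needed, because the model to be promoted is already planned.
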